Due to its natural and traditional origin, CYT’s development is characterized by an unusual history, and standard preclinical research to establish the optimal dosage, which would normally precede randomized clinical trials, was not carried out. To assess CYT pharmacokinetics, many studies were conducted in animal models; however, pharmacokinetic data in humans are limited (24). Nevertheless, findings gathered from these studies revealed that the half-life of CYT is approximately 4.8 h, with 95% being eliminated through urine unmodified (25, 26). A further important aspect of CYT’s pharmacokinetics is that there is no hepatic metabolism, and it is possible to exclude drug–drug interactions (27). The West dosing schedule (1.5 to 9 mg/day for 25 days) has been licensed for CYT in several countries, and it was used in an observational study in which participants treated with CYT had significantly high quit rates to suggest efficacy (7).

According to West et al. in 2011, CYT treatment is generally well tolerated. In fact, in this clinical trial, CYT is not associated with an increased risk of adverse events compared to placebo, although gastrointestinal symptoms are more frequent than placebo. The most frequent adverse reactions reported are abnormal dreams, insomnia, changes in taste, dry mouth and throat, decreased appetite, and, less frequently, nausea. Some patients have experienced headaches and irritability on the initial day of treatment. It is also noted that elevated doses of CYT can lead to dizziness and muscle weakness. However, reducing the dosage has been shown to alleviate these side effects. Importantly, CYT does not induce psychophysical alterations, making it suitable for individuals who drive vehicles or operate machinery (28, 29).

In Italy, the use of CYT is promoted by the Veneto regional program “Coordination and development of the Veneto system of tobacco treatment” for active smokers, especially those who smoke more than 15 cigarettes per day and are both available and motivated to quit smoking.

Since 2016, the galenic laboratory of HPs in the Integrated University Hospital of Verona (IUHVR), Veneto (Italy), has provided 1.5 mg CYT galenic capsules for in-hospital treatment for patients.

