#### Exclusion criteria

Patients who do not fit all of the requirements mentioned above, those who have any contraindications for the use of CYT, such as reported hypersensitivity to CYT, pheochromocytoma, malignant hypertension, unstable angina, will be excluded from the study, as will women who are breastfeeding, pregnant or likely to become pregnant during CYT treatment and are not willing to use an effective form of contraception.

Until the baseline visit, the use of other forms of nicotine delivery, such as electronic cigarettes, in combination with industrial cigarettes, will not be an exclusion criterion. However, the use of nicotine-containing products as smoking cessation medications (e.g., NRTs) starting from the QD will cause the exclusion of participants from the study, while the use of co-adjuvants for smoking cessation (e.g., electronic cigarettes without nicotine, Nirdosh®) will be allowed, according to clinical practice, and will be recorded in eCRF at each visit.

Because CYT is eliminated through urine unmodified, patients with chronic kidney failure will be closely monitored but not excluded from the trial. Patients in stage IV or V, with glomerular filtration rate (GFR) < 29 mL/min, will receive CYT treatment with halved dosage; patients in stage III, with GFR between 30 and 59 mL/min, will receive standard CYT treatment, but close patient monitoring will be performed.

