### Participant recruitment

Participating ward staff will be used to screen for and determine eligible participants, by physicians trained in the study by the principal investigator (PI) or sub-investigators (Sub-I), such as addiction medicine physicians (AMPs) or CM. Once potential participants are identified, ward staff will refer all current smokers interested in quitting smoking to the CM. Each patient’s eligibility for the study will be determined by the AMPs in collaboration with the CM, taking into account the patient’s current medical status and any contraindications to the usage of CYT.

The CM will then approach eligible patients, describe the CITOSP trial’s details to each potential participant, and answer any questions. If patients are willing to participate, prior to completing the baseline interview, written informed consent will be obtained.

Each participant will receive an anonymized study code at the baseline interview, and baseline data will be collected. This data will include general demographics such as age, gender, highest level of education, and current job position. Detailed medical histories will be considered, including medical conditions, current and remote anamnesis, and concomitant medications. Additionally, information on the participant’s smoking habits will be reviewed, such as age at smoking onset, cigarettes smoked per day, and previous attempts at quitting. Furthermore, the level of cigarette dependence assessed using the Fagerström Test for Cigarette Dependence (FTND) Questionnaire will be collected. The FTND is a validated and widely used questionnaire consisting of six items that measure the degree of nicotine dependence in tobacco smokers. The FTND yields a final total score ranging from 0 to 10. The patient’s physical nicotine dependence is closely related to the FTDN score. Scores from 0 to 2 indicate very low nicotine addiction; scores 3 and 4 indicate low nicotine addiction; a score of 5 indicates an average nicotine addiction; scores 6 and 7 indicate high nicotine addiction; and scores from 8 to 10 indicate very high addiction (32).

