The decision concerning the patient’s inclusion in the study will ultimately be made by the AMPs and the CM based on the predefined inclusion and exclusion criteria. Any participant who meets the exclusion criteria will not be recruited. Following the collection of baseline data, the AMPs and the CM will then give CYT, prepared by IUHVR’s HPs, to the participants and provide detailed counseling. In case of discharge, CYT will be provided to the patients to continue the therapy at home. CYT will be provided throughout the treatment duration according to the West dosing schedule (25 days, 101 capsules). In the case of patients with chronic kidney failure (stage IV or V), a reduced dosage schedule will be followed, providing 57 capsules.

On the first day of therapy, all participants will be instructed to abstain from smoking and to quit completely (quit day, QD).

Instructions about the West dosage schedule, common CYT ADRs, and emergency contact information will be given to participants by the CM. Finally, a study diary will be provided to support participants to help ensure proper intake of CYT.

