### Cytisine dosing schedule

The West dosing schedule consisted of six 1.5 mg capsules per day (one capsule every 2 h) for 3 days (days 1 to 3), five capsules per day for 9 days (days 4 to 12), four capsules per day for 4 days (days 13 to 16), three capsules per day for 4 days (days 17 to 20), and two capsules per day for the final 5 days (days 21 to 25) (see Table 2). The target quit date was scheduled for the first day of treatment (day 1) (7).

**Table 2 tab2:** West dosing schedule (7).

Day of treatment	N° of capsules/die	Frequency of administration
Days 1–3	6	1 capsule every 2 h
Days 4–12	5	1 capsule every 2.5 h
Days 13–16	4	1 capsule every 3 h
Days 17–20	3	1 capsule every 4 h
Days 21–25	2	1 capsule every 6 h

In the case of patients with stage IV or V chronic kidney failure, the CYT dosing schedule consisted of three 1.5-mg capsules per day for 12 days (days 1 to 12), two capsules per day for 8 days (days 13 to 20), and finally one capsule per day for the last 5 days (days 21 to 25) (see Table 3).

**Table 3 tab3:** Cytisine dosing schedule adapted to patients in stage IV or V chronic kidney failure.

Day of treatment	N° of capsules/die	Frequency of administration
Days 1–12	3	1 capsule every 4 h
Days 13–20	2	1 capsule every 6 h
Days 21–25	1	1 capsule every 12 h

Concomitant medication use during CYT treatment will be allowed, evaluated, and documented at each visit, and any possible interactions with CYT will be verified.

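### The reduced renal schedule is tied to chronic kidney failure, so an enrolled inpatient with acute impairment at the same GFR falls under the 101-capsule default

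*Protocol article*

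**What the plan says.** The Introduction gives the pharmacokinetic basis: a half-life of about 4.8 h, "with 95% being eliminated through urine unmodified". Exclusion criteria turns this into a rule: "Because CYT is eliminated through urine unmodified, patients with chronic kidney failure will be closely monitored but not excluded from the trial". The cut-off comes next: "Patients in stage IV or V, with glomerular filtration rate (GFR) < 29 mL/min, will receive CYT treatment with halved dosage". Stage III (GFR 30 to 59 mL/min) keeps the standard dose with close monitoring.

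Participant recruitment states the general supply: "CYT will be provided throughout the treatment duration according to the West dosing schedule (25 days, 101 capsules". It then makes a single exception: "In the case of patients with chronic kidney failure (stage IV or V), a reduced dosage schedule will be followed, providing 57 capsules".

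Cytisine dosing schedule repeats the restriction in its text, "In the case of patients with stage IV or V chronic kidney failure, the CYT dosing schedule consisted of three 1.5-mg capsules per day", and in the title of Table 3.

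On entry to the study, Participant recruitment has the physicians weigh the patient's "current medical status and any contraindications to the usage of CYT". It adds that the final decision on inclusion will "ultimately be made by the AMPs and the CM based on the predefined inclusion and exclusion criteria". The listed contraindications contain no renal item, acute or chronic, but the list is introduced as examples.

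**The concern.** The rule is narrower than its own reason. If the dose is lowered because the kidney removes the drug unchanged, what counts is how well the kidney works while the drug is taken, not how long it has been impaired. The population is hospital inpatients, in whom a low GFR can be acute. The article names acute renal impairment nowhere, whether as an exclusion, a reason to adjust the dose or a reason to monitor.

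The primary objective is safety in hospitalised smokers, and the Introduction says that use in such patients, with their co-morbidity and multiple medicines, has not been studied. It also links higher doses to dizziness and muscle weakness that ease when the dose is reduced. A dosing rule that gives the larger dose at a GFR where the protocol itself asks for the smaller one is therefore worth correcting. The close-monitoring clause has the same limit: an acute GFR of, say, 45 mL/min does not trigger it as printed.

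**Working it through.** **Inputs.** Daily capsule counts from Tables 2 and 3; 1.5 mg per capsule (Cytisine dosing schedule); stated totals of 101 and 57 capsules (Participant recruitment); Visit 1 on day 7, the first scheduled adverse-event assessment (Visits and follow-ups, Table 1).

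**Stated totals reproduced.**
- West schedule: 3×6 + 9×5 + 4×4 + 4×3 + 5×2 = 18 + 45 + 16 + 12 + 10 = 101 capsules; 101 × 1.5 = 151.5 mg.
- Reduced schedule: 12×3 + 8×2 + 5×1 = 36 + 16 + 5 = 57 capsules; 57 × 1.5 = 85.5 mg.

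Both match the article.

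**Who gets which schedule below the cut-off (printed as GFR < 29 mL/min).**

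| Enrolled patient | Printed rule that applies | Capsules |
|---|---|---|
| Chronic kidney failure, stage IV or V | Named exception | 57 |
| Low GFR newly measured, chronic disease not previously recognised | Same exception, through the GFR cut-off | 57 |
| Low GFR from acute impairment | No exception; general supply sentence | 101 |

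**Difference between the two schedules.**
- Whole course: 101 − 57 = 44 capsules, or 66 mg; 101/57 = 1.77; 57/101 = 56.4%.
- By day: the ratio is 6/3 = 2.0 on days 1–3, 5/3 = 1.67 on days 4–12, 4/2 = 2.0 on days 13–16, 3/2 = 1.5 on days 17–20 and 2/1 = 2.0 on days 21–25.
- Days 1–7: standard 3×6 + 4×5 = 38 capsules (57 mg); reduced 7×3 = 21 capsules (31.5 mg); 38/21 = 1.81. The excess is 17 capsules, or 17/44 = 38.6% of the whole-course excess, by the first scheduled adverse-event assessment.

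These figures compare two printed schedules. They do not measure exposure in blood, risk, or the number of patients concerned.

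**The case against.** The strongest reply is that the three sections agree with one another, and that a journal article leaves the handling of acute illness to the full protocol. This stands in part: the full protocol may cover the case. But the point is not a missing detail. The article prints the rule, its reason, its cut-off and the capsule counts, and it states the restriction to chronic disease in three sections.

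A second reply is that physicians would not enrol such a patient, or would not give the full dose. Current medical status is weighed, the contraindications are open-ended, and basing inclusion on the predefined criteria brings that open-ended list with it. This stands as a reason why the case should be uncommon. It does not close the gap, because the discretion concerns entry. Once the patient is enrolled, or if the impairment arises during the 25 days, no printed rule lowers the dose.

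A third reply is that the GFR figure could be applied to anyone below it. The sentence follows directly on chronic kidney failure and uses its stages, and the other two sections write the restriction out. If the wider reading was meant, the amendment only makes it explicit.

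A reader might go further and infer that the plan will overdose inpatients, or that the incidence of adverse events will be biased. The documents support neither. They give no frequency of acute impairment, no exposure data by GFR, and nothing to show that the confidence interval or sample size would change.

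**Conclusion.** The point holds as a scope error in a printed dosing rule. Taken literally, two enrolled participants with the same GFR below the cut-off receive 101 and 57 capsules according to whether the impairment is acute or chronic, a ratio of 1.77 over the course and 2.0 on days 1–3. The case is likely to be uncommon, the number affected could be zero, and any excess harm cannot be derived. It is a cheap patient-safety improvement in a study whose primary objective is safety, not a flaw in the analysis.

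The conclusion assumes that the article's wording is the operative rule, and that the general supply sentence applies to every enrolled patient outside the one exception. If the full protocol already doses by current GFR, only the article's wording is at fault.

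**What to change.** In Exclusion criteria, Participant recruitment and Cytisine dosing schedule (with the title of Table 3), replace the restriction to chronic kidney failure stage IV or V with: *GFR below the stage IV/V threshold, whatever the cause, by the most recent value before the first dose*. Then state that:

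1. these patients receive the reduced 57-capsule schedule by default;
2. the physician may defer the start if recovery is expected;
3. if GFR is found below the threshold during the 25 days, the reduced daily dose for that day of treatment applies from then on;
4. close monitoring covers any GFR below 60 mL/min, whatever the cause.

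The cost is a wording amendment in three sections and two eCRF fields, for the GFR value used and its date. This assumes that GFR is available from routine ward tests, which the existing GFR bands already imply. No new dose, capsule or visit is needed. Deferral leaves the visit plan intact because visits are counted from the quit day, which is the first day of treatment. A deferred start may, however, fall after discharge and need a handover. The downside is that some patients with transient impairment get a lower-dose or delayed course, which may lessen their benefit.

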## Methods

### Objectives of the study

The primary objective of the study is to assess the safety of CYT treatment in hospitalized smokers admitted to IUHVR.

The secondary objectives of this study are to assess patient’s compliance with CYT treatment and the efficacy of CYT treatment.

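### The printed GFR cut-off for the halved cytisine dose (< 29 mL/min) leaves out 29 to <30 mL/min, which the protocol's own stage IV/V rule includes; it should read < 30 mL/min

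*Protocol article*

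**What the plan says.** The protocol article enrols smokers with impaired kidney function on purpose and gives its reason for caution under Exclusion criteria: "Because CYT is eliminated through urine unmodified, patients with chronic kidney failure will be closely monitored but not excluded from the trial". It then states two numeric bands. For the more severe group: "Patients in stage IV or V, with glomerular filtration rate (GFR) < 29 mL/min, will receive CYT treatment with halved dosage". For the moderate group: "patients in stage III, with GFR between 30 and 59 mL/min, will receive standard CYT treatment", with the addition "but close patient monitoring will be performed".

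Elsewhere the reduced schedule is assigned by stage alone, with no GFR figure. Participant recruitment says: "In the case of patients with chronic kidney failure (stage IV or V), a reduced dosage schedule will be followed, providing 57 capsules". The text of Cytisine dosing schedule introduces the reduced regimen with "In the case of patients with stage IV or V chronic kidney failure", and the title of Table 3 is "Cytisine dosing schedule adapted to patients in stage IV or V chronic kidney failure".

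**The concern.** The two numeric bands do not meet. The lower one is a strict inequality that stops below 29, and the next starts at 30. This is more than a matter of decimals, because the whole-number result 29 is itself left without a dose by number. If GFR is reported in whole numbers, the cut-off should read ≤ 29 or < 30. If decimals are reported, it should read < 30. As printed it is wrong in both cases.

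The figure matters because it is the only numeric cut-off the article gives for the reduced schedule. Someone turning the rule into a dispensing check or a data-entry check would take the number from this sentence, and such a check would not trigger the reduced schedule at 29. The drug is cleared unchanged by the kidney, and safety is what the study is about: "The primary objective of the study is to assess the safety of CYT treatment in hospitalized smokers admitted to IUHVR".

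**Working it through.** **Inputs.** From Exclusion criteria: halved dose if GFR < 29 mL/min; standard dose with close monitoring (stage III) if GFR is 30 to 59 mL/min. From Participant recruitment: 101 capsules for the standard course and 57 for the reduced course. From Cytisine dosing schedule (Tables 2 and 3): the daily capsule counts, at 1.5 mg per capsule.

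**Step 1: reproduce the capsule totals.**
- Standard: 6×3 + 5×9 + 4×4 + 3×4 + 2×5 = 18 + 45 + 16 + 12 + 10 = 101 capsules; 101 × 1.5 mg = 151.5 mg.
- Reduced: 3×12 + 2×8 + 1×5 = 36 + 16 + 5 = 57 capsules; 57 × 1.5 mg = 85.5 mg.

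Both totals match the article. The schedules are not in question.

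**Step 2: apply the numeric rule as printed, then with the cut-off at < 30.**

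| GFR (mL/min) | By printed number | With cut-off < 30 |
|---|---|---|
| 28 | halved | halved |
| 28.9 | halved | halved |
| 29 | neither | halved |
| 29.5 | neither | halved |
| 29.9 | neither | halved |
| 30 | standard | standard |
| 59 | standard | standard |

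The gap is 29 ≤ GFR < 30. It is 1 mL/min wide and contains one whole-number value.

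**Step 3: apply the stage rule to the gap.** Stage III starts at 30 in the article's own sentence. A patient with kidney failure and a GFR of 29 is below stage III, so the stage label places that patient in stage IV. Exclusion criteria, Participant recruitment, Cytisine dosing schedule and the Table 3 title all then give the reduced schedule. The number and the label in the same sentence therefore disagree at 29 to <30, and the cut-off of 29 does not follow from the stage III lower bound of 30.

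**Step 4: size of a dosing error in the gap, if one occurred.** 101 − 57 = 44 capsules; 44 × 1.5 mg = 66 mg over 25 days.

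**The case against.** The strongest reply is that the protocol doses by stage, not by number. The places that set capsule supply and the daily regimen carry no GFR figure, and in the disputed sentence the figure reads as a gloss on the stage. No place in the article gives the standard dose at a GFR of 29, and the stage III band excludes 29 by number. A clinician who follows the stage label doses correctly, so the slip is one of description and not two rules prescribing different doses.

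Most of this stands. It settles what was intended and keeps the point small: the 66 mg difference describes an error that the document does not direct anyone to make. It does not make the printed number right. A stated threshold for a dose decision should agree with the rule it describes, and this is the only number on offer.

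A reader might also infer a matching fault at the top of stage III, because a GFR of 59 to <60 lies outside the printed 30 to 59 band. The document does not support that as a finding. The dose does not depend on it, no whole-number value is left out, and the general sentence in the same section already places all patients with chronic kidney failure under close monitoring.

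**Conclusion.** The point holds as a minor correction to a dosing threshold. The printed cut-off of < 29 mL/min is inconsistent with the stage III lower bound of 30 in the same sentence, and it leaves out a band that the stage IV/V rule covers.

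The conclusion rests only on the article's own bands and stage labels. The article gives no GFR distribution, so the number of participants affected cannot be calculated; with a band 1 mL/min wide it is likely to be small.

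A reader might go further and infer that patients at 29 are meant to receive the standard course, or that the renal dosing design is unsound. Neither follows. The stage label points to the reduced course, and both schedules add up to the capsule counts stated. The sample size, the planned confidence intervals and the endpoint definitions are unaffected.

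**What to change.** In the Exclusion criteria sentence on stage IV or V, replace < 29 mL/min with < 30 mL/min. Values from 29 to just under 30 then fall in the reduced-dose group, 30 stays in stage III, and the number agrees with the stage rule in Participant recruitment and Cytisine dosing schedule. If the site reports GFR only in whole numbers, ≤ 29 mL/min does the same, but < 30 is safer because it also covers decimals.

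The cost is one numeric edit in one sentence. Capsule supply, data collection, sample size and analysis do not change. If the printed figure has been copied into a dispensing or data-entry check, that check should be changed to match.

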### Participant recruitment

Participating ward staff will be used to screen for and determine eligible participants, by physicians trained in the study by the principal investigator (PI) or sub-investigators (Sub-I), such as addiction medicine physicians (AMPs) or CM. Once potential participants are identified, ward staff will refer all current smokers interested in quitting smoking to the CM. Each patient’s eligibility for the study will be determined by the AMPs in collaboration with the CM, taking into account the patient’s current medical status and any contraindications to the usage of CYT.

The CM will then approach eligible patients, describe the CITOSP trial’s details to each potential participant, and answer any questions. If patients are willing to participate, prior to completing the baseline interview, written informed consent will be obtained.

Each participant will receive an anonymized study code at the baseline interview, and baseline data will be collected. This data will include general demographics such as age, gender, highest level of education, and current job position. Detailed medical histories will be considered, including medical conditions, current and remote anamnesis, and concomitant medications. Additionally, information on the participant’s smoking habits will be reviewed, such as age at smoking onset, cigarettes smoked per day, and previous attempts at quitting. Furthermore, the level of cigarette dependence assessed using the Fagerström Test for Cigarette Dependence (FTND) Questionnaire will be collected. The FTND is a validated and widely used questionnaire consisting of six items that measure the degree of nicotine dependence in tobacco smokers. The FTND yields a final total score ranging from 0 to 10. The patient’s physical nicotine dependence is closely related to the FTDN score. Scores from 0 to 2 indicate very low nicotine addiction; scores 3 and 4 indicate low nicotine addiction; a score of 5 indicates an average nicotine addiction; scores 6 and 7 indicate high nicotine addiction; and scores from 8 to 10 indicate very high addiction (32).

The decision concerning the patient’s inclusion in the study will ultimately be made by the AMPs and the CM based on the predefined inclusion and exclusion criteria. Any participant who meets the exclusion criteria will not be recruited. Following the collection of baseline data, the AMPs and the CM will then give CYT, prepared by IUHVR’s HPs, to the participants and provide detailed counseling. In case of discharge, CYT will be provided to the patients to continue the therapy at home. CYT will be provided throughout the treatment duration according to the West dosing schedule (25 days, 101 capsules). In the case of patients with chronic kidney failure (stage IV or V), a reduced dosage schedule will be followed, providing 57 capsules.

On the first day of therapy, all participants will be instructed to abstain from smoking and to quit completely (quit day, QD).

Instructions about the West dosage schedule, common CYT ADRs, and emergency contact information will be given to participants by the CM. Finally, a study diary will be provided to support participants to help ensure proper intake of CYT.

